#### Analytic plan

In this trial, there are several levels of clustering: repeated observations are nested within the child/caregiver, the child/caregiver is nested within the team, teams are nested within the region, and regions are nested within CBAs. Therefore, we will use a modeling strategy that includes random intercepts for region and/or CBA, team, and random child/caregiver effects (intercept, slopes, as appropriate). All primary analyses will be conducted on an intent-to-treat basis using a generalized linear mixed-effects models framework [103], which can accommodate continuous, binary, and count outcomes through an appropriate choice of link function. Preliminary analyses will involve examining the outcomes and covariates to verify their appropriateness, identifying patterns of missing data, and conducting a multivariate outlier analysis. Model validation will be carried out using both analytical and graphical techniques to check core assumptions such as linearity, distribution, and homoscedasticity. Transformations of outcome variables will be considered if suggested by the model validation analyses. All analyses will include available relevant biological variables, including child or caregiver sex and age and baseline characteristics if there is any evidence of randomization imbalance in them. Randomization should produce intervention and control groups that are comparable and balanced. As a first-order check on confounding, we will examine the success of randomization by comparing baseline characteristics of children, caregivers, and providers assigned to the two study arms. Where clinically significant differences are apparent, child-, caregiver-, and provider-specific covariates will be added to the statistical models as fixed predictors to examine whether the intervention effect is robust in their presence.

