#### Primary and secondary outcomes

The analytic approach for each primary and secondary outcome measure will follow the same general model-building strategy. For outcomes assessed at baseline, 6 months, and 12 months, the models will include fixed effects for time (baseline, 6-, and 12-months), group, and their interaction, as well as covariates (e.g., child/caregiver sex, age, etc.) and random effects for child/caregiver, team, or region to account for clustering. The interaction between time and group will directly test the hypothesis that participants in the ESDM group show greater improvement than those in the EBI group. In all models, we will consider adding relevant covariates related to child/caregiver or provider-level characteristics if randomization at the region level did not ensure comparability between the two groups [108].

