#### Moderation analyses

Moderation analyses will explore the differential effectiveness of the two interventions by maternal level of education (as a proxy for SES), child race/ethnicity, and technician ESDM fidelity. We will build upon the primary models with treatment group by time effects by incorporating interaction terms for moderators of interest and conducting sub-group analyses. For each target moderator (e.g., maternal education), we will add the 3-way treatment group by time by moderator interaction term (and all lower-order 2-way and main effects) to determine whether differences between treatment groups in change over time for a given outcome variable are modified by target moderators. A significant 3-way interaction effect will indicate the presence of treatment effect heterogeneity between subgroups. Following this, we will conduct simple effect analysis to estimate treatment effect differences (i.e., difference in changes over time between arms) within each subgroup. For adherence to ESDM fidelity at the technician level, we expect substantial differences between treatment groups, and plan to investigate this as a moderator of all child outcomes.

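### As the primary model reads, covariates are added without covariate-by-time terms, so the planned robustness check can hardly move the tested group-by-time effect

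*Protocol article*

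**What the plan says.** Under Primary and secondary outcomes, the Protocol article specifies that "the models will include fixed effects for time (baseline, 6-, and 12-months), group, and their interaction, as well as covariates". The hypothesis test is the interaction: "The interaction between time and group will directly test the hypothesis that participants in the ESDM group show greater improvement". Baseline is therefore a level of the time factor, and the baseline score is a response and not a predictor.

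Covariates are described in two places. The Analytic plan says "All analyses will include available relevant biological variables, including child or caregiver sex and age and baseline characteristics", the last of these where imbalance is seen. It then says of clinically significant differences between arms that "covariates will be added to the statistical models as fixed predictors to examine whether the intervention effect is robust in their presence". The section on outcomes adds that "we will consider adding relevant covariates related to child/caregiver or provider-level characteristics if randomization at the region level did not ensure comparability".

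Interactions with covariates are spelled out only under Moderation analyses, as an extension of the primary models: "we will add the 3-way treatment group by time by moderator interaction term (and all lower-order 2-way and main effects").

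The framework is otherwise flexible. It has "random intercepts for region and/or CBA, team, and random child/caregiver effects (intercept, slopes, as appropriate") and a generalized linear mixed model "which can accommodate continuous, binary, and count outcomes through an appropriate choice of link function".

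**The concern.** The stated purpose of the added covariates is to learn whether the intervention effect survives adjustment. The intervention effect is a difference in change. A covariate that is fixed over time and enters as a main effect acts on the level of all three scores and not on change. The adjusted and unadjusted interaction estimates would then agree by construction, and the agreement could be reported as robustness although nothing had been tested.

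Regions are randomised and are few. The constrained randomisation described under Design & Randomization uses insurance mix and size, not child age or cognitive level. Table 2 collects demographics and the Developmental Profile cognitive score at baseline only, so these are natural adjusting variables and are constant over time. If one of them predicts language growth and differs between arms by chance, the main-effect adjustment leaves the resulting shift in the tested effect where it was.

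**Working it through.** **1. The plan's own figure.** Power considerations states at least 80% power for d = 0.6 with 300 children, 100 teams and 20 centers, region ICC 0.05 to 0.1, team ICC 0.1 to 0.25 and 10% dropout. Take 10 regions, 50 teams and 135 children per arm, total variance 1 and a two-sided 5% test. For a comparison of follow-up means, the variance of an arm mean is region/10 + team/50 + (1 − region − team)/135.
- Least favourable ICCs: 0.1/10 + 0.25/50 + 0.65/135 = 0.0198. The SE of the difference is √(2 × 0.0198) = 0.199, and power is Φ(0.6/0.199 − 1.96) = 85.4% (81.3% with a t reference on 18 df).
- Most favourable ICCs: 0.05/10 + 0.1/50 + 0.85/135 = 0.0133, and power is 95.7% (93.5% with t).

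The stated lower bound is reproduced, and the present point does not touch it.

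**2. Algebra.** Write the score of child i at time t as

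Y(i,t) = μ(t) + α·g(i) + β(t)·g(i) + γ·x(i) + random effects + error,

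with β(baseline) = 0 and x constant over time. The change to 12 months is

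Y(i,12) − Y(i,0) = μ(12) − μ(0) + β(12)·g(i) + terms without x.

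The term γ·x has gone. If x truly affects change with slope δ, the estimate of β(12) is displaced by δ × (mean x in ESDM − mean x in EBI), and fitting γ does not remove this. A term δ(t)·x does.

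**3. Numerical check.** Simulated data had 300 children and 3 visits. Assumed values: true interaction 0.6, covariate imbalance 0.3 SD, effect on level 0.4, extra effect on 12-month change 0.2. The expected displacement is 0.3 × 0.2 = 0.06.

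| Setting | No covariate | Main effect | Covariate-by-time |
|---|---|---|---|
| Complete data, random intercepts | 0.7093 | 0.7093 | 0.6497 |
| 10% covariate-related dropout | 0.6551 | 0.6577 | 0.5984 |

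The differences along a row are what matter, because any Monte Carlo offset from 0.6 is common to the row.
- **Complete data:** adding the main effect changed the estimate by at most 4 × 10⁻¹⁶ in generalized least squares and 9 × 10⁻¹⁵ in REML, with or without random slopes. Adding covariate-by-time changed it by 0.7093 − 0.6497 = 0.0596, matching the expected 0.06. The main effect moved only the group main effect (0.131 to −0.019), which is not the tested term.
- **10% dropout:** the main effect shifted the estimate by 0.003 on average and 0.018 at most, against an SE of about 0.10.
- **Logit link:** the shift was 0.006 on average and 0.028 at most, on the log-odds scale.
- **Precision:** the least-squares SE was 0.1000 without the covariate, 0.1000 with the main effect and 0.1011 with covariate-by-time. There was no gain, because the assumed covariate explained little of the change.

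**4. Possible size.** Suppose simple allocation of 10 against 10 regions of 15 children, and a covariate with region ICC 0.05 to 0.10. The SD of a chance arm difference is √(2 × (ICC/10 + (1 − ICC)/150)), which is 0.151 to 0.179. With an assumed slope of 0.25 SD of change per SD of covariate:
- imbalance 0.15: 0.15 × 0.25 = 0.0375, and 0.0375/0.6 = 6%;
- imbalance 0.3 (about twice the SD): 0.3 × 0.25 = 0.075, and 0.075/0.6 = 12.5%.

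**The case against.** The best reply is that the article never says main effects only. Calling covariates fixed predictors may just mean fixed as opposed to random, a condensed article need not give each parameterisation, and a full plan may include covariate-by-time terms. This stands in part: the form of entry is inferred. The inference is still the natural one, because the article names interactions when it wants them and presents them as additions to the primary model. The point is also not missing detail. A purpose is stated, and the terms as listed cannot serve it.

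A reader might go further and infer that covariates cancel exactly in every planned analysis. The documents do not support that. Exact cancellation needs a time-constant covariate, an identity link and complete data. Other links and transformations are allowed, 10% dropout is expected, the APPL assigns five ordered phases, and a covariate such as age at visit or a replaced technician's characteristics could vary over time. The check is nearly empty for time-constant covariates and not provably empty for all. For the Vineland communication standard score an identity link is the natural choice.

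A reader might also infer that the plan does nothing about imbalance. That is too strong: with baseline as a response, the interaction already removes arm differences in outcome level. What remains is imbalance in predictors of growth. Such imbalance averages to zero over randomisations, so it is an error in the particular trial and not a systematic bias. The imbalance formula above also ignores the constrained allocation within agencies.

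Finally, a claim that useful precision is being lost is not supported. It depends on how strongly the covariates predict change, which the plan does not give.

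**Conclusion.** The point holds in a limited form. As the Analytic plan and Primary and secondary outcomes sections read, the robustness check compares two estimates that are identical (time-constant covariate, identity link, complete data) or nearly so (about 10% dropout, or a logit link). It cannot reveal or correct an effect of chance imbalance in predictors of growth. An error of about 0.04 to 0.075 SD (6% to 12.5% of d = 0.6) is an illustration. It rests on an assumed slope of 0.25 and an assumed imbalance of 0.15 to 0.3 SD, the upper value being about a two-SD event under simple allocation. Sample size and power stand. The wording should be corrected because an uninformative check on the primary outcome could be reported as reassurance.

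**What to change.** In the Analytic plan and under Primary and secondary outcomes, state that each adjusting covariate, including those brought in for the imbalance robustness check, enters with its main effect and its covariate-by-time interaction. Keep provider- and region-level covariates few, because regions are few.

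An alternative is to model the 6- and 12-month scores with the baseline score and the covariates as predictors. That is an ANCOVA estimator and not an equivalent of the change contrast. The two differ when baseline scores differ between arms, so choosing it would change the primary analysis and should be a deliberate decision.

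The recommended change costs wording and two extra coefficients per single-coefficient covariate (6 and 12 months), which is small with 300 children. It should not be justified by precision, since the gain may be negligible.

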#### Primary and secondary outcomes

The analytic approach for each primary and secondary outcome measure will follow the same general model-building strategy. For outcomes assessed at baseline, 6 months, and 12 months, the models will include fixed effects for time (baseline, 6-, and 12-months), group, and their interaction, as well as covariates (e.g., child/caregiver sex, age, etc.) and random effects for child/caregiver, team, or region to account for clustering. The interaction between time and group will directly test the hypothesis that participants in the ESDM group show greater improvement than those in the EBI group. In all models, we will consider adding relevant covariates related to child/caregiver or provider-level characteristics if randomization at the region level did not ensure comparability between the two groups [108].

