### Procedures and measures

Child and family level outcomes will be assessed at three time points by trained assessors naïve to intervention condition: Baseline (BL), 6 months, and 12 months post BL. Outcome data will be collected by administering a brief battery of measures via distance technology that includes interview and survey and assessments with caregivers and video recordings. All assessors will be experienced MA or PhD level clinicians and supervised by a licensed clinical psychologist with over 20 years of experience in assessing young autistic children. All data will be entered directly into secure computer systems. Interviewers and video coders will be naive to group status (ESDM or EBI). The primary outcome will be child social communication and language (caregiver report and observational coding). Secondary outcomes are: (1) adaptive behavior and cognitive gains, (2) progress toward goals; (3) quality of life; (3) caregiver use of NDBI strategies; (4) increases in caregiver competence. We will assess engagement of the identified treatment mechanisms: child social motivation and caregiver use of NDBI strategies. Measures, constructs, and timing are listed in Table 2. Commonly used measures are described briefly. Newer or less standard measures are described in more detail.

**Table 2 Tab2:** Assessments

Domain	Measure and description	Method	Timing		
			T1	T2	T3

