**Primary Outcomes**					
Language & Social Communication	Vineland Adaptive Behavior Scales-3 Communication Subscale	Caregiver Interview	X	X	X
	APPL	Direct Observation	X	X	X

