#### Power considerations

Given that the proposed analyses for primary outcomes will employ mixed effects modeling of clustered data to assess differences in changes from baseline between treatment groups, power analyses were conducted using Monte Carlo simulations of multi-level models in SAS (SAS Institute Inc., Cary, NC). Expected fixed effect values for effects of interest (e.g., treatment group by time interactions) were obtained from prior research on ESDM treatments and developmental change [109]. We assumed a range of plausible intraclass correlation coefficient (ICC) values for the random effects of child/caregiver dyad (0.3 to 0.5), team (0.1 to 0.25), and region (0.05 to 0.1) based on previous community intervention studies and pilot data and accounted for a 10% dropout rate. We used a type I error level of 5%.

Under each scenario, our proposed sample size of 300 children/caregivers, 100 teams, and 20 centers would provide at least 80% power to detect a standardized improvement in children’s social communication and language of *d* = 0.6. We assumed that 10% of children would not contribute any data; however, the participants who dropped out would have provided some data and will contribute to the analyses. Therefore, our calculations are conservative.

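### Two separately tested primary measures stand behind one research question, but the 5% level, d = 0.6 and 80% power are given once, with no measure or success rule attached

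*Protocol article*

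**What the plan says.** Procedures and measures words the primary outcome as one construct with two data sources: "The primary outcome will be child social communication and language (caregiver report and observational coding"). Under Primary Outcomes, Table 2 lists two instruments: the "Vineland Adaptive Behavior Scales-3 Communication Subscale", obtained by caregiver interview, and the APPL, a five-phase language rating coded from video. Both are taken at baseline, 6 and 12 months.

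The analysis section treats them separately: "The analytic approach for each primary and secondary outcome measure will follow the same general model-building strategy". In each model the group-by-time interaction is the test of benefit. The mediation section also speaks of primary outcome variables in the plural. The article describes no composite, joint test, ordering or success rule.

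Power considerations gives one set of figures. The error level is stated once ("We used a type I error level of 5"%). The sample is described as "our proposed sample size of 300 children/caregivers, 100 teams, and 20 centers", and the power claimed for it, at least 80%, is also given once. The effect size is attached to the combined construct, "social communication and language of *d* = 0.6", and no measure is named. The power is claimed under each scenario of the assumed ICCs: "child/caregiver dyad (0.3 to 0.5), team (0.1 to 0.25), and region (0.05 to 0.1").

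**The concern.** Research question 1 asks one thing: whether children in the ESDM arm grow faster in social communication and language than those in usual EBI. Two tests at an unsplit 5% can answer it in two unadjusted ways. If a positive result on either measure supports the claim, the error rate of the claim exceeds 5%. If both must be positive, the power for the claim is below the power of each test.

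The practical risk is a split result. The two instruments differ in kind: one is caregiver report, the other is coded from observation. One may reach significance while the other does not. The article then gives no verdict, and the favourable measure can carry the conclusion after the data are seen.

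**Working it through.** **Inputs from the article.** 300 children, 100 teams, 20 centers, 10% dropout, 5% level, d = 0.6, team ICC 0.1 to 0.25, region ICC 0.05 to 0.1 (all Power considerations). Equal allocation, 50 and 50 supervisors (Abstract). A mean of 5 supervisors per region (Design & Randomization), so 100 / 5 = 20 regions.

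**Assumptions.** Two-sided tests; total variance 1; 20 regions as the unit of inference, so 18 df; correlation between the two test statistics from 0 to 0.5, since none is given. The fixed effects and variances of the authors' simulation are not shown, so the power figures are approximate.

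**Step 1: reproduce the plan's figure for one measure.** Children analysed: 300 × 0.9 = 270, that is 2.7 per team and 13.5 per region. The design effect is

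DE = 1 + (2.7 − 1)(ICC_team + ICC_region) + (13.5 − 2.7) ICC_region, and SE = √(4 × DE / 270).

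At the least favourable ICCs (0.25 and 0.10): DE = 1 + 1.7 × 0.35 + 10.8 × 0.10 = 2.675, SE = √(10.7 / 270) = 0.199, and d / SE = 3.01. The noncentral t with 18 df gives 81.3% power at 5%. So the 80% floor is reproduced for one measure tested at 5%, with little to spare. At 2.5% the same calculation gives 71.2%.

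**Step 2: either measure suffices, each at 5%.** At correlation 0 the family-wise error is 1 − 0.95² = 9.75%. At correlation 0.5 (bivariate normal) it is 9.1%. The upper bound is 10%.

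**Step 3: both measures required, each at 5%.** At correlation 0 the power is the square of the one-measure power:

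| Team ICC | Region ICC | One measure | Both, correlation 0 |
|---|---|---|---|
| 0.10 | 0.05 | 93.5% | 87% |
| 0.25 | 0.05 | 90.2% | 81% |
| 0.10 | 0.10 | 85.0% | 72% |
| 0.25 | 0.10 | 81.3% | 66% |

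In the last row, simulating pairs of t statistics gives 70% at correlation 0.5. Two of the four corners stay above 80% and two fall below it. As a check that does not use my SE: if one-measure power is exactly 80%, requiring both gives 0.80² = 64% at correlation 0 and 69% at 0.5.

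**Step 4: how often the result is split.** In the last row, with a true d = 0.6 on both measures, exactly one is significant in 2 × 0.813 × 0.187 = 30% of trials at correlation 0, and in 23% at correlation 0.5.

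**Step 5: what Holm would do in the same row.** Family-wise error is at most 5%. The chance that at least one measure passes is 92% to 86% (correlation 0 to 0.5), and per-measure power is about 78% to 77%.

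**The case against.** Much of the case on the other side stands.

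- **Per-measure reading.** A reader might infer that no reading of the primary outcome carries both stated figures. The article does not support that. Read per measure, each test has 5% and at least 80%. Holm with success on at least one measure also meets both figures in Step 5, although the plan states no such rule.
- **The meaning of 5%.** A reader might also infer that a false claim of benefit is nearly twice as likely as the plan states. That goes too far. The 5% is an input to the power simulation and is never called family-wise, and the article does not say that either measure suffices. The 9% to 10% is conditional on that rule.
- **80% is a floor.** Requiring both measures keeps power above 80% at two of the four ICC corners. What remains is that the article claims its floor under every scenario.
- **The power model.** My SE is for a single contrast and does not use the child ICC, whereas the authors simulated change from baseline. In a random-intercept change model the region, team and child intercepts cancel. With residual share 0.55, SE = √(8 × 0.55 / 270) = 0.128, and power is 99.3% per measure and about 98.7% for both. The number of regions matters too: with 20 agencies of at least two regions each there would be 40, giving 92.5% per measure and 0.925² = 86% for both at the least favourable ICCs. The 66% to 70% therefore cannot be put forward as the trial's power. The error figures in Step 2 do not depend on any of this.
- **Left to the SAP.** A multiplicity procedure may well sit there, and its absence here is not the finding. But the article itself fixes what is primary and what the power statement covers. It names two separately tested measures, one claim, and one unsplit level with no measure attached.

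**Conclusion.** The point holds in a limited form. The 5%, d = 0.6 and at least 80% can be true of each measure taken alone. As the basis for the single claim in research question 1, they do not hold together under either unadjusted rule across all the plan's scenarios. If either measure suffices, the error of that claim is about 9% to 10% for correlations between 0.5 and 0. If both are required, error stays at or below 5%, but power at the least favourable ICCs is approximately 66% to 70%; at more favourable ICCs it exceeds 80%.

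The error figure rests only on two tests at an unsplit 5% and the assumed correlation. The power figure also rests on 20 regions, 18 df, a unit-variance contrast and d = 0.6 on both measures, and a change-score model could give a much higher value.

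**What to change.** Choose one of two rules and state it in the analytic plan.

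1. Test Vineland-3 Communication and the APPL with Holm at a family-wise 5%, and limit the claim to the measure or measures that pass.
2. Name one of them as the sole primary measure and make the other key secondary. This keeps a single test at 5%, provided the power figures were derived for the measure chosen.

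In either case, say in Power considerations which measure and which success rule the 5%, d = 0.6 and 80% describe. If Holm is chosen, the authors should re-run their own simulation and report per-measure power and the power for at least one measure; my figures should not be adopted in its place.

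The cost is a sentence or two and, under Holm, one more simulation run and slightly lower per-measure power (about 81% to 77–78% in my approximation at the least favourable ICCs). No extra participants or data are needed.
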